### Data collection, management, and analysis methods

For retention of patients, appointment reminders will be scheduled, and question-answering sessions will be planned. The complete follow-up will be mentioned in the patient file, and if patients are required to withdraw or discontinue, the patient file will be closed and maintained for the record purposes.

Observations will be made after the completion of the study, according to the data collected with the help of the following:
I.Case registration form with detailed history and examinationsII.Follow-up assessment proforma

The principal investigator and co-investigator will do data monitoring and coding. Data entry will be done in soft copy and case record form in hard copy. The values will be verified twice before submission in soft copy. Each file of the patient is secured with a specific patient code.

The data obtained will be calculated using the Student’s Paired ‘t’-test and Unpaired ‘t’ test for objective variables with
SPSS statistical software.

*To verify the significance of the results*

Improvements in Fugl-Meyer assessment-35%, one leg stance test-20%, functional reach test-35%, quality of life scale-25%, Barthel index-25% and NIH stroke-scale-score-20% will be considered as significant.

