**Methods:**

A total of 40 patients will be enrolled and divided randomly into two equal groups. In Group A (control), standard treatment (modern + physiotherapy) will be prescribed for one month. In Group B (interventional group),
*Dashmoola Basti* will be added to the aforementioned standard treatment for one month.

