### Sample size

Due to practical considerations such as cost, patient inconvenience, judgments not to proceed with an investigation or a lengthy study duration, the number of participants in the study is restricted. So for the phase-I trial, 20 sample size is considered for each group.
^
3
^

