### Eligibility criteria

The inclusion criteria for the study are the patients with the first stroke diagnosed with CT/MRI (thrombolytic stroke only) without other neurological deficits but < six months of onset, patients diagnosed as stroke with ICD code 2020 ICD-10-CM Diagnosis Code I69.351 patients between 45 to 60 years of age irrespective of gender/occupation and socio-economic status. Patients with controlled hypertension and Non-insulin dependent Diabetes Mellitus (NIDDM). Patient with ankle dorsiflexion stage 1 to 2 and ankle plantar flexors spasticity 1+ on. Patients are willing to give informed consent and ready to follow simple instructions.

The exclusion criteria for the study are the patients having a thrombolytic stroke with onset for > six months, subjects with complications such as uncontrolled metabolic disorders and severe systemic disorders, e.g., renal or cardiac failure, altered sensorium, or coma. Those who are on tube feeding or intravenous fluid therapy. The patients of stroke with a history of trauma (
*Abhighatajanya*), onset due to intracranial space-occupying lesions, post-surgical or postpartum complication, degenerative disorders of the brain or intracranial infectious disease or hemorrhagic nature. The patients with specific medical and psychological contraindications for electrical stimulation Brooks,
^
4
^ patients with visual or auditory difficulties, anti-anxiolytic treatments. Pregnant women and lactating mothers will also be excluded. Patients contraindicated for
*Basti & Swedana* therapy and patients with fixed ankle or foot contracture, pacemakers, and a metal plate in the lower limb will be excluded.

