### Participant timeline

•For physiotherapy (five days weekly for one month)•
*Karma Basti* (alternate regime of
*Niruha Basti* with
*Dashmoola Kwatha* and
*Anuvasana Basti* with
*Dashamoola* oil for complete one month, i.e., Day 1
^st^–Day 30
^th^)

Time schedule of enrolment: Patients with the first Stroke diagnosed with CT/MRI (thrombolytic Stroke only) without other neurological deficits but <6 months of onset will be enrolled for the study.

Interventions (including any run-ins and washouts): There are no washout periods; the intervention of Panchakarma treatment and Physiotherapy sitting for 30 days.

Assessments and visits for participants: Assessment will be carried out at baseline level and after the intervention, i.e., on the 30
^th^ day, then follow-up visits on the 60
^th^ and 90
^th^ day.

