### Assignment of interventions (for controlled trials)

Patients will be recruited by simple randomization through the computer-generated table. The principal investigator (PI) and co-investigator (CO-I) will allocate and enroll the patient. Using computer-generated random numbers, the researcher creates random allocation cards. The researchers will keep the original randomly assigned sequences in a safe place and use a different copy to sign up the patients.

The envelopes will be marked with serial numbers on the outside. The date, time, patient ID, post-procedure results, and other required details will be on the envelope.

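### The plan names within-arm paired t-tests and an unadjusted unpaired t-test without saying which is the main analysis; an ANCOVA on the baseline already collected is more precise than either form of the unpaired test

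*Protocol article*

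**What the plan says.** The section on data collection, management and analysis states: "The data obtained will be calculated using the Student’s Paired ‘t’-test and Unpaired ‘t’ test for objective variables". No other test is named in the article. The same section then lists percentage improvements per scale (for example 35% for Fugl-Meyer, 25% for Barthel) that will count as significant, without reference to the other arm.

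Under Study design the trial is described as a two-arm superiority trial. The Participant timeline says: "Assessment will be carried out at baseline level and after the intervention", that is on day 30, with follow-up on days 60 and 90. So a baseline value exists for the assessed scales. On size: "So for the phase-I trial, 20 sample size is considered for each group". On allocation: "Patients will be recruited by simple randomization through the computer-generated table", with no blocking or stratification stated. Eligible patients have had a first stroke "but < six months of onset".

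**The concern.** A superiority claim needs one between-arm comparison. The plan puts a within-arm test and a between-arm test side by side and ranks neither. Both arms receive drug treatment plus the same physiotherapy, and patients are less than six months from stroke. Improvement in both arms is therefore plausible without any effect of the added Basti. If the paired results carry weight, the trial can appear positive for that reason alone.

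The second issue is precision. The group size was set by practical limits, so information per patient matters. An unpaired test on post-treatment scores leaves out the baseline value. One on change scores uses it, but with a fixed coefficient of 1 instead of the coefficient the data support. ANCOVA estimates that coefficient.

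**Working it through.** **Inputs from the article:** 20 per arm; baseline and day-30 scores; paired and unpaired t-tests; superiority objective. The sample size has no stated alpha, power, effect or SD, so there is no planned figure to reproduce.

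**Assumed, because not stated:** two-sided 5% level; equal SDs at baseline and day 30, set to 1; exactly 20 per arm; baseline-outcome correlation ρ from 0.3 to 0.8.

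**Variance of the arm difference, relative to the post-score t-test**
- Post scores: 1
- Change scores: 2(1 − ρ)
- ANCOVA: (1 − ρ²) × (1 + 1/36). The last factor is the expected cost of estimating one slope with 40 patients, about 3%.

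| ρ | Change | ANCOVA | ANCOVA ÷ post | ANCOVA ÷ change |
|---|---|---|---|---|
| 0.3 | 1.40 | 0.91 × 1.028 = 0.935 | 94% | 67% |
| 0.5 | 1.00 | 0.75 × 1.028 = 0.771 | 77% | 77% |
| 0.7 | 0.60 | 0.51 × 1.028 = 0.524 | 52% | 87% |
| 0.8 | 0.40 | 0.36 × 1.028 = 0.370 | 37% | 93% |

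Break-even points: ANCOVA beats post scores when (1 − ρ²) × 37/36 < 1, so ρ > √(1/37) = 0.16. It beats change scores when (1 + ρ)/2 × 37/36 < 1, so ρ < 35/37 = 0.95.

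**Power at a true difference of 0.65 SD, ρ = 0.7.** This uses the noncentral t with noncentrality 0.65 × √(20/2) / √(relative variance).
- Post: 0.65 × 3.162 / 1 = 2.06, 38 df, power 52%
- Change: 2.055 / √0.60 = 2.65, 38 df, power 73%
- ANCOVA: 2.055 / √0.524 = 2.84, 37 df, power 79%

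**Difference detectable with 80% power (SD units; post / change / ANCOVA):** ρ 0.3: 0.91 / 1.08 / 0.88; ρ 0.5: 0.91 / 0.91 / 0.80; ρ 0.7: 0.91 / 0.70 / 0.66; ρ 0.8: 0.91 / 0.58 / 0.55.

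**Validity.** In 20,000 simulated trials per setting with no arm difference, the type I error was about 5% for all three between-arm tests.

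**Baseline imbalance.** The difference in baseline means has SD √(2/20) = 0.316. The chance that it exceeds 0.3 SD in either direction is 2 × [1 − Φ(0.3/0.316)] = 34%. At ρ = 0.7, a 0.3 SD imbalance shifts the expected post-score difference by 0.7 × 0.3 = 0.21 SD. It shifts the change-score difference by (1 − 0.7) × 0.3 = 0.09 SD in the opposite direction. ANCOVA removes the shift in expectation.

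**Paired tests when the arms do not differ (20 per arm, 19 df)**
- Both arms change by 0.8 SD of change: each test is significant with probability 0.924; both, 0.924² = 85%.
- Both arms change by 0.5: each 0.564; both, 0.564² = 32%; exactly one, 2 × 0.564 × 0.436 = 49%.

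**The case against.** The strongest reply is that the plan does contain a sound between-arm test and may already use baseline. The paired test uses it by construction. The percentage thresholds are framed as improvements, which points to an unpaired test on changes. On that reading a claim that baseline is ignored would be wrong, and imbalance would be over-corrected, not left alone. This stands. The gain from ANCOVA at ρ = 0.7 is then 73% to 79% power. The larger step from 52% applies only to post scores, the less supported reading.

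Three further inferences are tempting but not supported.
- That the unpaired test is invalid: its type I error is at the nominal level.
- That the authors intend to contrast two paired p-values: the article does not say so. It only leaves that route open by not ranking the tests.
- That the ordinal modified Ashworth scale will be t-tested: the t-tests are limited to objective variables, a term left undefined, and that scale has no percentage threshold.

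It is also fair that the article gives no correlation or expected change, so every size above is conditional. Covariate choice is often left to an analysis plan. But here the article does name its tests, and that choice can be reviewed.

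**Conclusion.** The point holds as one of efficiency and clarity. The stated methods do not identify the analysis that answers the superiority question, and the paired tests cannot answer it. On either reading the unpaired test is less precise than a baseline-adjusted ANCOVA across correlations of 0.3 to 0.8. The variance saving is 6% to 63% against post scores and 7% to 33% against change scores, depending on the correlation. A reader might conclude that the planned between-arm test is wrong or that baseline is discarded. The article supports neither.

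The sizes rest on equal SDs, 20 per arm, a two-sided 5% level and assumed correlations. The paired-test figures rest on assumed standardised changes of 0.8 and 0.5. The ordering of the methods changes only below a correlation of about 0.16 (against post scores) or above about 0.95 (against change scores).

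**What to change.** State that the between-arm analysis of each continuous outcome is an ANCOVA of the day-30 score on arm and baseline score, reported as an adjusted difference with a 95% CI. State that paired within-arm changes are descriptive and carry no inference about the added treatment. Time since stroke onset may be added as a prespecified covariate.

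This changes analysis wording only. It needs no extra patients, visits or measurements. Each covariate costs one degree of freedom and, if it proves uninformative, about 3% of variance with 40 patients. The change does not settle the choice among several primary outcomes, the handling of ordinal scales or the analysis of days 60 and 90.

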### Variables to be measured

Improvements in the following assessment variables are expected as primary outcomes: Fugl-Meyer assessment for sensory-motor function of lower extremities, one-leg stance test, functional reach test for static and dynamic balance in patients, quality of life scale and Barthel index independent living of patients with Stroke, resistance experienced during passive range of motion based measured on Modified Ashworth scale NIHSS for improvements in clinical features of stroke are expected to be measured.
^
7
^

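### The percentage cut-offs for significance have no stated denominator or unit, and read as change from baseline they make the verdict depend on the starting score as well as the gain

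*Protocol article*

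**What the plan says.** The protocol article, under Data collection, management, and analysis methods, names paired and unpaired t-tests and then adds a separate rule for judging significance: "Improvements in Fugl-Meyer assessment-35%, one leg stance test-20%, functional reach test-35%, quality of life scale-25%, Barthel index-25% and NIH stroke-scale-score-20% will be considered as significant".

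Under Variables to be measured, these instruments are listed as primary outcomes. They include "quality of life scale and Barthel index independent living of patients with Stroke", the lower-extremity Fugl-Meyer, stance, reach and NIHSS. Under Participant timeline, assessments fall at baseline and day 30, with follow-up at days 60 and 90.

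The rule leaves several things open:
- the denominator (own baseline, group mean or scale maximum);
- the unit (patient or group);
- the comparison (within or between arms);
- the visit;
- its relation to the t-tests that precede it.

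No range or step size is given for any scale. Eligibility criteria require a certain degree of ankle impairment but put no limit on the baseline Barthel, Fugl-Meyer or NIHSS score.

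**The concern.** This is a decision rule on primary outcomes, not a detail left for later. A 25% improvement between a baseline and a later visit would ordinarily be taken as change divided by baseline. On that metric the points required rise in proportion to the starting score, while on a rising capped scale the points available shrink as the start rises. Above some level the target cannot be reached at all.

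Two patients, or two groups, with the same gain can therefore receive opposite verdicts because of where they began. A patient who ends at the top of the scale can be recorded as not significantly improved. Because denominator and unit are left open, the choice made at analysis can also settle the result.

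**Working it through.** There is no power or sample-size figure tied to these cut-offs to reproduce: the Sample size section sets 20 per group on practical grounds. The check is algebra on the stated percentages.

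**Inputs from the protocol article.** Cut-offs c: Fugl-Meyer 35%, stance 20%, reach 35%, quality of life 25%, Barthel 25%, NIHSS 20%.

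**Assumptions.** Barthel 0-100 in 5-point steps; Fugl-Meyer in 1-point steps with a maximum of 28, 34, 86 or 100; NIHSS in whole points, falling to a best value of 0.

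**1. Ceiling, per patient, percentage of own baseline.** With baseline b and maximum M, full recovery fails when (M - b)/b < c, that is, when b/M > 1/(1 + c).
- 25% rule: 1/1.25 = 0.800 of maximum.
- 35% rule: 1/1.35 = 0.741 of maximum.

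Barthel 85 to 100: 15/85 = 17.6%, fails; starts of 90 and 95 fail too. Barthel 80 to 100: 20/80 = 25%, just passes. For Fugl-Meyer, full recovery fails from a baseline of 21 (maximum 28), 26 (maximum 34), 64 (maximum 86) or 75 (maximum 100).

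**2. Low start, per patient.** One step s passes when s/b ≥ c, that is, when b ≤ s/c.
- Barthel: 5/0.25 = 20, so 20 to 25 passes (5/20 = 25%).
- Fugl-Meyer: 1/0.35 = 2.86, so one point passes only from a baseline of 1 or 2.

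**3. NIHSS.** Full recovery is b/b = 100% from any start, so there is no ceiling. Baseline dependence remains: one point is enough from 5 (1/5 = 20%), while a start of 20 needs four (4/20 = 20%).

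**4. Stance and reach.** The document states no cap, so only baseline dependence can be shown. The quality-of-life instrument is not named, so its range and direction are unknown.

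**5. Other readings.**
- Percentage of scale maximum: full recovery fails when b/M > 1 - c, that is, above 75% (25% rule) or 65% (35% rule). A single step never passes on the Barthel and Fugl-Meyer ranges above.
- Percentage change in group means: a 15-point Barthel gain is 15/57 = 26.3% from a mean of 57 (passes) and 15/63 = 23.8% from 63 (fails).

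**6. Illustration under assumed distributions** (Barthel as above, 400,000 simulated patients per scenario, one common gain of mean 15 and SD 10). None of these distributions is in the document.
- With baseline mean 50 to 70 and SD 15 to 20, the share starting above 80 runs from about 1.5% to 26%.
- The rule is met by about 79% of those starting at 40 or below, 60% from 45-60, 40% from 65-80, and none above 80.
- With baseline mean 60 and SD 20, the average of patient percentages is 28.7% (passes 25%), while the percentage computed on group means is 22.9% (fails).

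**The case against.** The strongest reply is that the article never says the percentages are of each patient's own baseline. The rule stands beside t-tests and could equally be a criterion on group means, in which case no single-patient example applies. On a percentage-of-maximum reading, the example of one small step passing disappears. This is right, and the point is conditional for that reason. But neither alternative frees the rule of the starting level: the group-mean reading reverses its verdict between means of 57 and 63, and the percentage-of-maximum reading makes full recovery fail from lower starts still.

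A reader might also infer that full recovery can fail on every listed outcome. The document does not support that. The ceiling is shown only for rising capped scales such as Barthel and Fugl-Meyer, on assumed ranges. It does not arise for NIHSS, and no cap is stated for stance or reach. The low-start effect on Fugl-Meyer is very narrow.

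A further inference would be that chance baseline imbalance will appear as a treatment difference in success rates. The article plans no comparison of success rates; its between-group method is the unpaired t-test. In the assumed scenarios a 6-point baseline difference moves the success rate by 6 to 7 percentage points, less than half the sampling error of such a difference with 20 per arm (√(2 × 0.25/20) = 0.158, about 16 points).

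Finally, the ankle criterion in Eligibility criteria may keep some patients from starting near the top of the lower-extremity Fugl-Meyer. How many start high cannot be known from the document.

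**Conclusion.** The point holds in conditional form. The article lets percentage improvements decide significance without a denominator or unit. On the ordinary change-from-baseline reading, the verdict depends on the starting level as well as the gain.

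The limits of 80% and 74% of maximum follow from the stated cut-offs alone for any rising capped scale scored from zero. The Barthel and Fugl-Meyer score examples rest on assumed ranges and steps, and the simulated shares on assumed distributions. For NIHSS, stance and reach only baseline dependence is established. The number of patients affected is unknown, so no claim is made that the trial's overall result would change. The case for acting is that a primary-outcome criterion can return opposite answers for equal gains and that correcting it is cheap.

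**What to change.** In Data collection, management, and analysis methods, remove the percentage cut-offs as the criterion of significance. Base the conclusion on the between-arm difference in absolute score (points for the scales, seconds for stance, centimetres for reach), using the unpaired test already planned. In these units a 15-point gain counts as 15 points from any start.

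Keep any threshold only as a reference value in scale units, stated in advance, for interpreting that difference. It should not serve as a per-patient pass mark: a fixed 15-point Barthel mark would still fail 90 to 100. If percentages are still reported, state the denominator and unit and label them descriptive.

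Redefining the percentage as a share of the achievable gain is not a cure, because it mirrors the problem: 95 to 100 scores 5/5 = 100%, while 20 to 35 scores 15/80 = 18.75%.

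The cost is one reworded sentence before analysis, with no new data, visits or patients. The small downside is that the sponsor must choose and justify a reference value for each instrument.

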## Introduction

In clinical practice, stroke has been very notorious for impeding the continuity of life and day-to-day activities. It is the most common example of such a crippling disorder. On extensive review of contemporary literature, it is observed that, despite massive worldwide efforts in this science to rectify early results in reducing the risk of death or disability, it is disappointing.
^
1
^ Partial recovery is obtained after a particularly long time. Moreover, it is observed that there are certain limitations, contra-indications, or side effects of currently established treatment modalities for stroke.
^
2
^

Considering the complicated and critical nature of the disease, i.e., stroke, it becomes imperative to search for safe, promising, and effective treatment modalities in alternative sciences for early rehabilitation purposes for stroke. Though most of the studies suggest that the individual use of
*Panchakarma* therapy, external oleation (
*Bahya Snehana*), sudation therapy (
*Swedana*) along with medicated enema (
*Basti*) and conventional physiotherapy, i.e., Motor Relearning Programme (MRP), and the combination of electrical modality with Functional Electrical Stimulation (FES) shows promising results in the rehabilitation of patients with stroke.

However, no study has been carried out to assess their combined effects on the therapeutic outcome of the rehabilitation of such patients. Moreover, the research is also required to determine the MRP and FES combined effect of supporting stroke patients for improving knee extension and gait parameters. Therefore, this study is proposed to generate clinical evidence showing excellent post-stroke recovery within a short time in restoring gross and fine movements to the maximum extent quicker.

The study aims to analyze and compare the adjuvant role of
*Dashmoola Basti* with standard treatment in stroke rehabilitation. In addition, the efficacy of physiotherapy (MRP and FES) in rehabilitating stroke patients will be assessed. The study’s goal is to assess and compare the adjuvant role of
*Dashmoola Basti* with standard control over sensorimotor function of lower extremities in stroke patients using the Fugl-Meyer assessment, as well as to assess and compare the adjuvant role of

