### Study design

It is an interventional study, it is a superiority clinical trial, i.e., randomized reference standard control open-labeled two-arm comparative clinical trial.

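### Percentage improvements are labelled significant without reference to the control group, and the protocol does not say how this rule relates to the planned t-tests

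*Protocol article*

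**What the plan says.** The Study design section states that "it is a superiority clinical trial", randomised, open-label and with two arms. The Introduction gives the aim as comparing the adjuvant role of Dashmoola Basti "with standard treatment in stroke rehabilitation". The question is therefore what Basti adds to care that both arms receive.

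The section on data collection, management and analysis names the tests: "The data obtained will be calculated using the Student’s Paired ‘t’-test and Unpaired ‘t’ test for objective variables". Directly after this, under the line "To verify the significance of the results", comes a second criterion. It begins "Improvements in Fugl-Meyer assessment-35%, one leg stance test-20%, functional reach test-35" per cent, and ends "quality of life scale-25%, Barthel index-25% and NIH stroke-scale-score-20% will be considered as significant".

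The thresholds are thus 35% for Fugl-Meyer, 20% for one-leg stance, 35% for functional reach, 25% for quality of life, 25% for the Barthel index and 20% for the NIH stroke scale. The text does not say:

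- which group must reach them, or whether Group A enters the comparison;
- whether a group mean or an individual patient is judged;
- which visit counts (the Participant timeline has assessments at baseline and days 30, 60 and 90);
- what happens when the percentages and the t-tests disagree.

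**The concern.** A superiority claim needs a contrast between the arms. An improvement of a stated percentage is most naturally a change from a patient's or a group's own baseline, and that quantity does not involve Group A.

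In this trial such a change can be expected without Basti. The Eligibility criteria admit patients less than six months after stroke, when recovery is still plausible. The Interventions section gives both arms modern treatment plus the motor relearning programme and functional electrical stimulation, five days weekly for one month. The Discussion itself expects this shared physiotherapy to improve mobility, strength and walking.

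Group B could therefore pass a threshold, and the result be reported as significant, although Group A did equally well. The chance of this would depend on how much both arms recover, and no error rate set in advance would control it. The paired t-test has the same weakness, because it also asks only whether a group changed from its own baseline.

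**Working it through.** **No figure to reproduce.** The protocol article gives no alpha, power, effect size or SD. The group size is set on practical grounds: "So for the phase-I trial, 20 sample size is considered for each group". The calculation below therefore illustrates the consequence of the rule and does not check a stated number.

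**Inputs from the protocol.** n = 20 per group; thresholds of 20%, 25% and 35%.

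**Assumptions not in the protocol.** Basti has no effect, so both arms share a true mean improvement mu, taken from 10% to 40% of baseline. The SD of percentage change is 30 points, varied from 15 to 45. The rule is applied to the mean of Group B. The t-tests are two-sided at 5%.

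**Formula for the percentage rule.** P(Group B mean reaches threshold T) = 1 − Φ((T − mu) / (SD/√n)). With SD 30, SD/√n = 30/√20 = 6.71.

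- T = 35, mu = 10: (35 − 10)/6.71 = 3.73, probability about 0%.
- T = 35, mu = 25: (35 − 25)/6.71 = 1.49, probability 7%.
- T = 35, mu = 35: 0, probability 50%. This follows for any SD, because the mean lies on the threshold.
- T = 20, mu = 10: (20 − 10)/6.71 = 1.49, probability 7%.
- T = 20, mu = 25: (20 − 25)/6.71 = −0.75, probability 77%.

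| Shared improvement mu | T = 20% | T = 25% | T = 35% |
|---|---|---|---|
| 10% | 7% | 1% | about 0% |
| 25% | 77% | 50% | 7% |
| 35% | 99% | 93% | 50% |
| 40% | above 99% | 99% | 77% |

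Both arms have the same distribution here, so Group A reaches each threshold equally often.

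**Sensitivity to the SD.** At mu = 25%, moving the SD from 15 to 45 takes the 20% threshold from 93% to 69%, and the 35% threshold from 0.1% to 16%. At mu = 10%, it takes the 20% threshold from 0.1% to 16%, while the 35% threshold stays below 1%.

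**Paired t-test in Group B alone.** Chance of significance ≈ Φ(mu/(SD/√n) − 1.96). With SD 30:

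- mu = 10: Φ(1.49 − 1.96) = 32%.
- mu = 20: Φ(2.98 − 1.96) = 85%.
- mu = 25: Φ(3.73 − 1.96) = 96%.

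A significant paired test in Group B is therefore likely at moderate shared recovery with no Basti effect.

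**Unpaired t-test.** The shared mean cancels in B minus A, so the false-positive rate does not depend on mu. In 20,000 simulated trials at each of mu = 25%, 35% and 40% (SD 30, 20 per arm), the test was significant in 5.1% to 5.3%, and in favour of Group B in 2.5% to 2.8%. The theoretical value in that direction is 2.5%.

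**The case against.** The strongest reply is that a between-group test is planned. The unpaired t-test stands in the sentence just before the percentages, and the objectives in the Abstract and Introduction are framed as comparisons with standard control. A reader might infer that the percentages are the only decision rule, or that the trial ignores its control group. The document does not support that. What it lacks is any statement of which criterion governs.

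The before-after reading, though natural, is also an inference. The percentages may have been meant as thresholds of clinical relevance read alongside the t-tests, or as differences between the arms. This stands as a caution. But the line above the percentages ties them to significance, and nothing in the text gives either alternative meaning.

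The probabilities depend on assumed recovery and SD. At 10% shared recovery the rule is seldom met, and the 35% threshold practically never. The figures show only that the error rate moves with the natural course. The proper comparison for a claim in favour of Group B is about 2.5%, not 5%, and the protocol states no alpha.

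A reader might also object that percentage change is undefined from a zero baseline, or out of reach near the top of a bounded scale. Those objections presuppose a rule applied patient by patient, which the document does not state. The ceilings would also need scale maxima that it does not give. They are not relied on here.

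Finally, the trial is small and is called phase I in the Sample size section. That does not remove the problem, because the Study design section still claims superiority.

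**Conclusion.** The concern holds in this form: the protocol article states a significance rule that bypasses its own planned between-group test and gives no order between the two. Taken as before-after improvement, neither the rule nor the paired t-test can support the superiority claim, because natural recovery and shared physiotherapy can satisfy both in Group B.

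That conclusion follows from the design and does not depend on the illustrative figures. Under the stated assumptions (no Basti effect, 20 patients, SD 30 points), the chance of meeting a threshold runs from about 0% to above 99% as shared recovery goes from 10% to 40%, against about 2.5% for an unpaired test favouring Group B.

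It would go too far to say that the trial will be declared positive when Basti adds nothing. That would follow only if the percentages override the unpaired t-test, and the document leaves this open. The gap should be closed before results are seen, because it bears on the trial's main claim.

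**What to change.** Replace the paragraph on verifying significance with wording to this effect:

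- Superiority is judged only by the difference between Group B and Group A, with its 95% CI, on a primary outcome and at a time point that the sponsor names in advance. The choice of outcome and visit is the sponsor's.
- Paired tests within a group are descriptive and support no claim about Basti.
- The six percentages are kept, if at all, as descriptive targets, or as responder thresholds with the proportion of patients reaching them compared between the arms.

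This costs one paragraph and needs no new data or visits. The drawback for the sponsor is that the success criterion becomes harder to meet.
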